#### 2.5.2. Study Procedure

The study is schematically depicted in Figure 2. Data will be collected from participants before and after the intervention, using a specific questionnaire designed in order to evaluate the program (Appendix A Table A1). Due to the young age of the children, some limitations when reading and answering a questionnaire are expected, and so they will complete it in parts, thus avoiding the possible discomfort that a long questionnaire may generate in them. The pre-questionnaire part of each session will be completed at the beginning of the corresponding session and the post-questionnaire at the end of this session. They will have to complete a third questionnaire one month after the intervention in order to assess the maintenance of the acquired knowledge and behaviour. 

The pre- and post-intervention questionnaires will be completed with the help of 2–3 members of the research group, in addition to the school responsible teacher. They will help them to understand the questions they have to answer, always avoiding any influence. One month after the intervention, the post-questionnaire will be completed again with the help of the schoolteachers.

The control group will consist of a similar number of students to the intervention group; they will be part of the same school and their socio-demographic characteristics will be similar, even if they will be in the final year of the cycle. They will continue with the normal school curriculum. Students in the control group will be asked to complete a questionnaire as the intervention group, and they will have to answer it in the same month in which the intervention of the other group is being carried out. They will be helped by their teachers to understand the questions if necessary and will have to complete it in one session, since the aim is to avoid altering the usual routine of their classes.

Upon completion of the intervention, parents or guardians will be requested to fill out an online questionnaire to gather their feedback on the project as well as their children’s opinions, as reported by the parents.

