### 2.5. Intervention

#### 2.5.1. Intervention Design

This nutrition education program is adapted to the curriculum of the Spanish schools. The intervention will consist of 8 sessions and the main goals will be (1) to understand the balanced diet and to apply it to one’s own diet, (2) to learn what CD and gluten are, and (3) to promote social inclusion of people with CD.

As aforementioned, it is an intervention based on competencies and respective learning outcomes. Therefore, to design the program, the first step was to define the competencies that children will develop during the intervention (Table 1). These competencies were then organised into learning outcomes, according to Bloom’s degree of cognitive abstraction [38,39] from level 1 to 6, and some activities were designed in order to develop these learning outcomes [40]. 

As mentioned, the teaching methodology chosen to develop learning outcomes is inquiry-based learning (IBL), which has proven to be very effective in science teaching–learning processes [41]. As a result, an inquiry-oriented teaching-learning process was developed, focused on facilitating children’s understanding of the research process. The teaching–learning process will be developed through games and experiments related to the topic of each session, described in Table 1. It must be noted that some topics will be transversally learnt along the intervention. In other words, content from some sessions will influence the achievement of various learning outcomes.

The whole intervention will last 4 weeks; 8 face-to-face sessions (one topic each) will be held during school hours, with 2 sessions per week (Table 2). Each session will last one hour. In addition to the session, each student will have to carry out several tasks at home together with their families, in relation to what they have learnt in class, to reinforce it through family involvement.

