### 2.6. Outcome Measures

#### 2.6.1. Primary Outcomes

Due to the fact that the present intervention is based on competencies and learning outcomes, the results are also proposed according to them, differentiating between knowledge-related results and those related to behaviour, which are more difficult to achieve. The primary outcomes are shown in Table 3. 

As mentioned, the primary outcomes will be measured by a pre- and a postquestionnaire reported by children at the beginning of the session, before the activities and discussion of the topic, and at the end of the session. They will be measured again one month after the intervention.

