### 2.8. Statistical Analysis

The description of the characteristics of the participants and data from the pre-, post- and retention test (one month after) questionnaires will be reported per group (control and intervention). 

For the analysis of the differences between groups, a variety of statistical tests will be used depending on the type of response to the questions (continuous, discrete or qualitative). Based on the distribution of the variables of interest in the sample, descriptive statistics for continuous data will be presented using the mean and standard deviation or the median and interquartile range. Qualitative data shall be presented as frequencies and percentages. Quantitative variables will be analysed using an ANOVA of repeated measures test using the group as a factor of the independent level (parametric) or Wilcoxon’s test segmenting by group (non-parametric). On the other hand, qualitative variables in two categories will be analysed with Chi-square and Cochran’s Q tests. Finally, qualitative variables in more than two categories will be analysed with Chi-square and McNemar Bowker’s tests.

Data will be entered and analysed using SPSS 28.0 software. A confidence interval of 95% and significance level of *p* < 0.05 will be assumed.

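### The two arms answer the primary-outcome questionnaire on different schedules and in different formats, and the part of this that varies over time biases the group-by-time contrast

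*Protocol article*

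**What the plan says.** **Intervention arm.** Section 2.5.2 splits the questionnaire by session because a long one may be uncomfortable for young children. The pre part for each session "will be completed at the beginning of the corresponding session and the post-questionnaire at the end of this session". Section 2.6.1 confirms that the primary outcomes are measured "at the beginning of the session, before the activities and discussion of the topic, and at the end of the session", and again one month after the intervention. Section 2.5.1 gives the session length: "Each session will last one hour". The pre and post questionnaires "will be completed with the help of 2–3 members of the research group, in addition to the school responsible teacher". At one month the help comes from schoolteachers.

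**Control arm.** Section 2.5.2 asks control children to complete a questionnaire as the intervention group does, and "they will have to answer it in the same month in which the intervention of the other group is being carried out". On help and format: "They will be helped by their teachers to understand the questions if necessary and will have to complete it in one session". The reason given is to leave the normal class routine undisturbed.

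**Analysis.** Section 2.8 states that data from the pre, post and "retention test (one month after) questionnaires will be reported per group (control and intervention"). Quantitative variables are to be analysed by repeated-measures ANOVA with group as the between-subject factor, or by a non-parametric alternative.

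The Discussion names non-randomisation and the age difference as weaknesses. It does not mention the difference in administration.

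**The concern.** A control group in a pre/post/follow-up design shows how scores move without the programme, through retesting, maturation and the circumstances of answering. It can do so only if both arms are measured at comparable times and in comparable ways. Here the interval, the format and the helpers all differ by arm, and in the intervention arm the helpers also change over time. A group difference in change may then partly reflect how and when the questionnaire was given. This timing applies to the primary outcomes generally, so none of them is protected.

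**Working it through.** No stated figure is at issue. The check sets the procedures side by side and asks which differences survive in the contrast.

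**Step 1. Procedure by arm**

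| | Intervention | Control |
|---|---|---|
| Format, pre and post | in parts, by session (2.5.2) | whole questionnaire, one sitting (2.5.2) |
| Pre-to-post interval | about 1 hour per topic (2.5.1, 2.5.2, 2.6.1) | not given in the text |
| Helpers, pre and post | 2–3 researchers plus teacher | teachers, if necessary |
| One month | schoolteachers | no date given in the text |
| Earlier related teaching before baseline items | yes, for later sessions | none from the programme |

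The last row follows from section 2.5.1, which says that content from some sessions bears on several learning outcomes. Table 1 marks the sessions that contribute transversally. For example, Day 3 (celiac disease) feeds the inclusion competence taught on Day 8.

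The retention interval is also uneven within the intervention arm. Table 2 spreads eight sessions over four weeks, and the third questionnaire comes one month after the end. The gap from post to retention is therefore about four weeks for Day 8 and nearly eight for Day 1.

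**Step 2. What cancels.** Write a(g,t) for the administration effect in group g at time t. The bias in the pre-to-post contrast is

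[a(I,post) − a(I,pre)] − [a(C,post) − a(C,pre)],

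and likewise for pre to follow-up. Take an assumed effect of 0.3 SD in the intervention arm and none that varies over time in controls:

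| Pattern in intervention arm (pre, post, follow-up) | Bias, pre to post | Bias, pre to follow-up |
|---|---|---|
| Constant format or helper effect (0.3, 0.3, 0.3) | 0 | 0 |
| Immediate recall at post only (0, 0.3, 0) | +0.3 | 0 |
| Researcher help at pre and post only (0.3, 0.3, 0) | 0 | −0.3 |
| Baseline raised by earlier sessions (0.3, 0, 0) | −0.3 | −0.3 |

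The last three patterns correspond to features the article describes. They act on different contrasts and with different signs, so the net direction is unknown.

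**Step 3. Illustration of consequence.** Suppose no true effect, and a net artefact b in SD of the change score. Use a two-sided 5% normal test with standard error √(2/n) per arm, ignoring clustering:

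P(reject) = 1 − Φ(1.96 − b/SE) + Φ(−1.96 − b/SE).

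At n = 60 per arm, SE = √(2/60) = 0.183. For b = 0.2, b/SE = 1.095 and P ≈ 0.195.

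| Assumed b | 60 per arm | 30 per arm |
|---|---|---|
| 0 | 5% | 5% |
| 0.1 | 8.5% | 6.7% |
| 0.2 | 19.5% | 12.1% |
| 0.3 | 37.6% | 21.3% |
| 0.4 | 59.1% | 34.1% |

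The arm sizes assume an equal split of the 120 and 60 participants in section 2.3. The values of b are assumptions, because the article gives no basis for choosing one.

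**The case against.** **Number of control waves.** A reader might infer that controls answer only once, so that the group-by-time effect cannot be estimated. The singular wording of section 2.5.2 allows this, but the document does not establish it. Controls are to complete a questionnaire as the intervention group does, section 2.8 reports all three time points for both groups, and Figures 1 and 2, which may mark control data collection, are not shown here. What stands is that the text is unclear on the number and timing of control waves.

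**Helpers.** The contrast is not researchers against teachers, since the teacher is also present in the intervention arm at pre and post. The difference is the added researchers, who belong to the team that delivers the programme. The article also says that helpers must avoid influencing answers. That is a fair safeguard against prompting, but it does not address interval or format.

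**Size.** A reader might divide an assumed helper or fatigue effect of 0.1–0.2 SD by the planned d = 0.32 and report a bias of 31–63%. That does not hold. The constant part of such an effect cancels, and section 2.3 does not say that 0.32 is a group-by-time effect.

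**Value of the control arm.** It would go too far to say that the control group then serves no purpose. If controls are measured at one month, both arms appear to have teacher help then, and that comparison is free of the one-hour interval. It is still weakened by the helper change since baseline and by the baseline items asked late.

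**Practical reasons.** Splitting the questionnaire suits young readers, and a single control sitting spares the timetable. These reasons explain the choices but do not remove the bias.

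**Conclusion.** The point holds. The article itself sets different schedules and formats by arm for the primary outcomes, then compares the arms over time. The within-hour interval, the helper change at one month in the intervention arm only, and the late baseline items vary over time, so they do not cancel in the group-by-time contrast. Direction and size cannot be determined from the document, and the error rates above depend on assumed artefacts. The conclusion rests on the text of sections 2.5.1, 2.5.2, 2.6.1 and 2.8. If the figures give control dates, the unclear number of waves would be settled, but the contrast between session-by-session and single-sitting completion would remain. This should be fixed before the study starts, because no later analysis can realign waves that were collected at different times and in different ways.

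**What to change.** For the outcome analysis, give the full questionnaire in both arms at the same three waves: before Day 1, after Day 8, and one month later. Use matching dates in the paired fifth- and sixth-year classes. Use the same format in both arms, split over the same days if one sitting is too long. Use the same type of helper, working from one script, at every wave. Keep the session-start and session-end items as process or formative measures only. State the number and dates of control waves in section 2.5.2 so that they agree with section 2.8.

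The cost is revised procedure wording, one longer sitting or two half sittings for the intervention children, and possibly additional teacher-supervised sittings for controls. The choice of helper needs thought. Teachers in the intervention classes are those who wished to take part (section 2.4), so they are not neutral either, and the common script matters for that reason. The Discussion places implementation in the near future, so the change can still be made.

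### The primary-outcome questionnaire is given in parts with researchers helping in one arm and in one sitting with teachers helping in the other, and single-wave comparisons cannot separate this from programme effect

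*Protocol article*

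**What the plan says.** Everything on this point stands in Section 2.5.2 of the protocol article.

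- **Why the form is split.** The protocol expects children this young to have some limits in reading and answering, and so "they will complete it in parts, thus avoiding the possible discomfort that a long questionnaire may generate in them".
- **Intervention group, timing.** "The pre-questionnaire part of each session will be completed at the beginning of the corresponding session and the post-questionnaire at the end of this session".
- **Intervention group, helpers at pre and post.** The questionnaires "will be completed with the help of 2–3 members of the research group, in addition to the school responsible teacher". These helpers explain the questions and are told not to influence the answers.
- **One month.** "the post-questionnaire will be completed again with the help of the schoolteachers". Researchers are not mentioned, and whether the form is split is not stated.
- **Controls.** Their teachers help with understanding if necessary, and the children "will have to complete it in one session, since the aim is to avoid altering the usual routine of their classes".

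Section 2.6.1 rests all primary outcomes on this questionnaire. Section 2.8 compares arms and waves by repeated-measures ANOVA with group as a factor, Wilcoxon within group, chi-square, Cochran's Q and McNemar-Bowker, with no allowance for how the form was given. The limitations in the Discussion name the lack of randomisation and the age difference, but not this.

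**The concern.** The protocol's reason for splitting the form concedes that length matters for these children. It then gives one arm the split form and the other the whole form. The reason given for controls is class routine; comparability is not discussed. Who helps also differs, and Section 2.1 says that the research team supplying helpers to the intervention group is the team that delivers the programme.

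Sittings and helpers are completely confounded with arm, so no covariate can separate them once the data are in. Shorter or skipped answers late in a long form, or answers shaped by who is in the room, would change scores without any change in knowledge or attitude. One primary outcome (Table 3) is attitude to science. Table A1 asks for agreement with a derogatory statement about researchers, which intervention children rate with researchers present and controls rate without them. By contrast, Section 2.6.2 has the parents' questionnaires completed with no member of the research group present.

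**Working it through.** The protocol gives no figure for this effect, so there is none to reproduce. The check compares the stated conditions, follows them through the planned tests, and adds an illustration.

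**1. Conditions as written (Section 2.5.2)**

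| | Sittings | Helpers |
|---|---|---|
| Intervention, pre and post | In parts, around each session | 2–3 researchers plus the teacher |
| Intervention, one month | Not stated | Schoolteachers |
| Control | One session | Their teachers, if necessary |

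The text does not describe the control procedure wave by wave. It speaks of a questionnaire answered during the intervention month, while Section 2.8 reports pre, post and retention data for each group.

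**2. Length of the form (Table A1)**

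Items by competence: 4 + 5 + 5 + 4 + 3 + 4 + 3 + 4 = 32. Open questions: 2 + 3 + 0 + 3 + 1 + 3 + 0 + 0 = 12. Over 8 sessions the intervention group answers 32/8 = 4 items per part on average; controls answer all 32 at once.

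**3. What each comparison carries**

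Let m_I be the shift from the intervention arm's conditions at pre and post, m_I' its shift at one month, and m_C the control shift. Shifts are taken as additive.

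- Between arms at pre or post: true difference + (m_I − m_C). The full mode difference enters a chi-square test at such a wave, and it also enters the group main effect.
- Group-by-time, pre to post: [(post_I + m_I) − (pre_I + m_I)] − [(post_C + m_C) − (pre_C + m_C)]. Both shifts cancel, provided that controls are measured at both waves under the same conditions.
- Post to one month within the intervention arm: true change + (m_I' − m_I). The change of helper stays in the Wilcoxon, Cochran's Q and McNemar-Bowker results. It also stays in a between-arm contrast if control conditions are constant.

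**4. Illustration of size (the shift b is assumed)**

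Section 2.3 gives 120 children, raised to 144. Split evenly, that is 60 or 72 per arm. With no true effect, two-sided 5% level, normal approximation and clustering ignored, the standard error is √(2/n) SD and

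P(p < 0.05) = 1 − Φ(1.96 − b/SE) + Φ(−1.96 − b/SE).

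For n = 72, SE = √(2/72) = 0.1667. At b = 0.1, b/SE = 0.6 and P = 0.087 + 0.005 = 0.092. For a shift at one wave only, the SE of a between-arm change is √[(2/n) × 2(1 − ρ)]. This equals the single-wave SE when ρ = 0.5.

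| Assumed shift b (SD) | Single wave, 60 per arm | Single wave, 72 per arm | Change, shift at one wave, ρ = 0.7, 60 per arm |
|---|---|---|---|
| 0.1 | 8.5% | 9.2% | 10.9% |
| 0.2 | 19.5% | 22.4% | 29.3% |
| 0.32 (the planning effect in Section 2.3) | 41.8% | 48.4% | 61.9% |

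The table shows what a given shift would do. It is not evidence that such a shift exists.

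**The case against.** Several points can fairly be made for the protocol.

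- **Help has the same stated purpose in both arms**, namely understanding the questions, and researchers are told to avoid influence. This stands as a safeguard on intent. It does not equalise the number of sittings or who is present.
- **A constant mode effect drops out of group-by-time**, and the ANOVA has group as a factor. This stands for pre to post if controls answer at both waves under unchanged conditions. It does not protect a single-wave test, a group main effect or the one-month comparison. Section 2.8 does not state at which wave chi-square is applied.
- **One sitting for controls is a deliberate trade-off** to spare class routine. This is a legitimate reason, but it does not deal with the effect on comparability.
- **Blocks on set days in both arms would disturb the design.** Sections 2.5.2 and 2.6.1 tie the intervention group's pre and post parts to the sessions. This stands, and the remedy should leave that timing alone.

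A reader might also infer that the one-month form is one long sitting, so that fatigue would look like lost retention. No sessions remain to split it over, but the text does not say so; only the change of helper is written. Nor does the text support saying that controls have a single adult present, since it speaks of teachers in the plural, or that their conditions are identical at every wave.

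**Conclusion.** The concern holds in limited form, and the plan should be changed. Sittings and helpers differ by arm, and the helper changes at one month in the intervention group. These differences can be read as programme effect in between-arm comparisons at a single wave, and the change of helper can be read as loss of retention from post to one month.

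The stronger reading, that every between-arm result is biased, is not supported, because a mode effect constant within each arm cancels in the group-by-time term. That cancellation assumes additive shifts and controls measured at pre and post under the same conditions.

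Size and direction cannot be derived from the protocol. The percentages under the working rest on assumed shifts, equal arms and no clustering.

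**What to change.** In Section 2.5.2:

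1. In both arms and at all waves, make the class teacher the only helper, reading from one written script limited to explaining the question. Researchers who deliver the programme give no help with the questionnaire.
2. Use the same format in both arms at one month, and state it.
3. Keep the session-linked pre and post parts for the intervention group. Where schools agree, let controls answer the same item parts in short slots instead of one session.
4. Where schools do not agree, add the one-sitting difference to the limitations and base the between-arm conclusion on the group-by-time contrast, not on single-wave tests.

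The cost is protocol wording, a one-page script, less researcher help for the children and possibly a few short slots in control classes. No staff are added. Some helper difference may remain, because Section 2.4 forms the intervention group from classes whose teachers wished to take part; the script limits this but does not remove it. The change has to be made before data collection, since analysis cannot separate conditions from arm afterwards.

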### 2.6. Outcome Measures

#### 2.6.1. Primary Outcomes

Due to the fact that the present intervention is based on competencies and learning outcomes, the results are also proposed according to them, differentiating between knowledge-related results and those related to behaviour, which are more difficult to achieve. The primary outcomes are shown in Table 3. 

As mentioned, the primary outcomes will be measured by a pre- and a postquestionnaire reported by children at the beginning of the session, before the activities and discussion of the topic, and at the end of the session. They will be measured again one month after the intervention.

